**Background**

**Etiology.** The vast majority of squamous-cell cervical cancer is now thought to be the long-delayed consequence of sexually transmitted oncogenic human papillomavirus (HPV) infection 33. Women progress from infection, to asymptomatic high-grade preinvasive dysplastic lesions and finally to invasive cancer. Important risk factors for progression to cervical neoplasia include persistence of oncogenic viral types 34-37 and high viral loads 38-40. Periodic screening offers many opportunities to discover and treat preinvasive lesions before cancer develops 41. Widespread screening in the US has been highly successful: a 70% decline in cervical cancer incidence and mortality has been noted in the last 5 decades 42.

**Burden of suffering.** An estimated 80% of the 466,000 case of invasive cervical cancer that occur each year are diagnosed among women in developing countries 43. From 1988 to 1992, Zimbabwe reported the highest rates (65-70 per 100,000 women) followed by areas of Brazil and Peru 43; rates in the United States over that same period ranged from 7 to 12 per 100,000. That cervical cancer is an important cause of morbidity and early mortality among women in the developing world is undisputed. Given that cervical cancer is largely a preventable disease, these statistics are discouraging. In 1995, cervical cancer accounted for 30% of all registered cancers and 80% of all gynecological cancers in Zimbabwe 44.

**Obstacles to cervical cancer prevention.** Lack of consumable supplies, qualified staff and access to curative surgical treatments are barriers to establishing effective screening programs in low-resource areas such as Zimbabwe 44, 45. Cytology-based programs pose particular quality-control and logistical problems, fostering recent interest in alternative screening programs based on detection of human papillomavirus DNA 46, 47 and visual inspection with acetic acid followed by cryotherapy 48. All secondary prevention programs, however, rely on providing access to screening modalities and interventions administered by trained personnel and implementation of cervical treatments that can be costly and have inherent risks to women.

**Evidence supporting barrier methods for cervical cancer prevention**. Another approach to cervical cancer control is development and adoption of interventions that decrease exposure to HPV. Despite evidence from observational studies suggesting that barrier contraceptives may provide protection, these methods have received little attention. In 1996, the US Preventive Services Task Force summarized evidence on primary prevention of cervical cancer 49. The Task Force found that use of barrier contraception (diaphragm and condoms) and spermicides (foam or contraceptive jelly) was associated with lower risk of invasive cervical cancer. Of 11 case-control studies and one cohort study examined, 10 reported that at least one of these methods of contraception was associated with a significantly lower risk. The protective effect persisted after controlling for the potential influence of age at first intercourse, cytology screening history and smoking. Substantial reductions in risk of invasive cervical cancer were observed among both condom users (odds ratios = 0.4-0.8) 50 and diaphragm users (OR = 0.2-0.7) 51, 52. A longer duration of use was associated with greater protection 50. A recent study indicated that longer duration of barrier method use decreased risk of cervical preinvasive lesions specifically among women positive for high-risk HPV types 53.

**Potential associations between HPV infection and HIV acquisition**. The immune system plays an important role in the natural history of HPV infection. Over 70 types of HPV have been identified, of which over 30 can infect genital epithelium. HPV infection occurs after genital contact and can result in a spectrum of disease encompassing genital warts, precancerous changes known as dysplasia, and invasive cancer. Typically, however, HPV infection is transient, clinically unapparent, resolves spontaneously, and results in subsequent protection against re-infection with that particular HPV type 37. These observations explain the excitement regarding potential HPV vaccines for preventing cervical cancer 54. Consistent with a pivotal role for the immune system in combating HPV infection are clinical observations that immunocompromised individuals are more likely to be infected with HPV, to harbor multiple HPV types, to develop precancer as a result of HPV infection, and to recur after therapy 55-58. The finding of dense infiltrates of lymphocytes in regressing genital warts also argues that the local immune response plays an important role in the natural history of genital warts 59. The immunological activity resulting from HPV infection may increase the risk of vaginal acquisition of HIV by increasing the local presence of immune cells susceptible to HIV infection.

The cervical transformation zone consists of the junction of two distinct epithelial surfaces, the columnar epithelium of the endocervix and the squamous epithelium of the ectocervix. The interface of 2 epithelial surfaces is a rare anatomic occurrence in the human body, and results in a biological phenomenon known as metaplasia, involving ongoing cellular transformation from columnar to squamous histology. Hence the transformation zone is a site of unique biological activity. Of particular relevance for this proposal is the finding that the majority of dysplasia caused by HPV occurs on the cervix, within 1 cm of the transformation zone. The transformation zone is also an active immunologic site capable of eliciting a robust secondary immune response. Germinal centers, which are sites of antigen presentation, B cell clonal proliferation, and T cell activation, are rare in normal cervical transformation zone but are abundant in association with high-grade dysplasia 60. A subset of germinal centers associated with dysplasia contains HPV antigens, indicating that the local immune response is directed in part against HPV. The [name] lab has also quantified local immune cell infiltrates in normal cervical transformation zone compared to areas of high-grade dysplasia and found high grade dysplasia contains significantly elevated numbers of CD4+ and macrophages than normal cervical epithelium. These results indicate that target cells of HIV infection are increased as a result of HPV-induced disease and suggest that HPV, like other STIs, might enhance the local susceptibility to HIV infection by recruiting susceptible immune cells to the site of infection.

**Unparalleled opportunity.** Given the absence of randomized, controlled trial data and the potential for confounding, the US Preventive Services Task Force concluded that evidence was insufficient to recommend for or against routine counseling of women about use of barrier methods for cancer prevention, although they recommended that women be informed about this potential benefit as part of contraceptive counseling. The straight-forward hypothesis that diaphragms will reduce HPV incidence and persistence can be readily tested and if substantiated, will provide a simple, affordable, readily available intervention to reduce the risk of cervical cancer for women worldwide.

**Methods**

This study will be offered to women enrolled in the Zimbabwe cohort of the diaphragm effectiveness trial (MIRA). Separate consent will be required to participate in this sub-study. Enrollees will be informed of the following additional testing to be performed (See Chart A: HPV study flow sheet). Neither study participants nor providers will be informed of HPV results nor will the results be used to direct clinical management.

• Enrollment visit: cytology and cervical swab for HPV testing

• 3 month visit: self-swab for HPV testing

• 6 month visit: self-swab for HPV testing

• 9 month visit: self-swab for HPV testing

• 12 month visit: self-swab and cervical swab for HPV testing

• 15 month visit: self-swab for HPV testing

• 18 month visit: self-swab for HPV testing

• 21 month visit: self-swab for HPV testing

• 24 month visit or last visit: cytology and cervical swab for HPV testing

**Cytologic sample collection and analysis:** At the time of the enrollment visit pelvic examination, a sample for cytology will be obtained from the endo- and ecto-cervix with a spatula and an endocervical brush. The specimen will be smeared onto a glass slide and then fixed immediately using hairspray (or another fixative). Cytology will be stained and interpreted in Zimbabwe where reliable cytology services have been available for the past 10 years (personal communication, [name]). Cytopathologists will be blinded to the arm of the study to which participants have been randomized.

**HPV sample collection:** At the enrollment visit, after the cytology sample is taken, the cervix and endocervix will be swabbed under direct visualization with a Dacron swab and stored in Sample Transport Medium (Digene Diagnostics, [name]) at 40C.. At follow-up visits, participants will be instructed in the technique of self-sampling and these samples will be stored in specimen transport medium as stated above. At the 12 month follow-up visit, a clinician-collected swab will be collected in addition to the self-collected swab. At study exit, a final clinician-collected swab will be obtained under direct visualization at the time of pelvic examination. Study exit will vary from 12 to 24 months depending on time of enrollment. Samples will be shipped to UCSF with cold packs for analysis in the laboratory of [name] by PCR using MY09/11 primers (see below). In addition, quantification of HPV levels will be performed by real-time PCR in HPV-positive samples from all women who sero-convert to HIV and a matched sample of controls who do not sero-convert. These will be reported as viral loads. Currently [name] laboratory has PCR primers and probes for quantitative PCR in HPV 16, 18 and 33-positive samples, and is developing assays for the remaining high risk HPV types.

**Secondary study outcome: Cervical dysplasia, biopsy-confirmed.** Women with abnormal Pap tests interpreted as AGUS, HSIL, adenocarcinoma in situ and cancer will be referred for immediate colposcopy. Women with Pap results of ASCUS or LSIL will undergo a repeat Pap smear after 6 months. If the results indicate ASCUS or worse, she will be referred for colposcopy. At the time of the exit Pap test, the threshold for referral will remain the same as at previous visits (cytologic abnormalities of AGUS, HSIL or worse). Women with exit Pap results of ASCUS or LSIL will be counseled and referred to local clinics for repeat Pap smears 6 months later. Colposcopists will be blinded to the arm of the study to which participants have been randomized. Women with colposcopic abnormalities will undergo diagnostic biopsies, and those with cervical intraepithelial neoplasia (CIN) 2 or 3 will undergo loop electrosurgical excision procedure. Women found to have cancer will be referred for cancer treatment. Histological analyses of biopsy and loop specimens will be performed in Zimbabwe. All colposcopic and histological data will be entered on a case report form and transferred to UCSF.

**Choice of tests: Cytology:** Two major methods by which cervical cytology is collected and prepared are currently used in research protocols: conventional cytology and liquid-based cytology. We will perform conventional cytology since the laboratory in Zimbabwe does not process liquid-based tests and is unlikely to do so in the near future. Also, liquid-based preparations have been shown in a randomized, controlled trial to increase the likelihood that a test will be wholly unsatisfactory and require a return visit and repeat pelvic examination 61. We would like to minimize return visits for this large number of participants.

**Choice of tests: HPV determination.** We will perform PCR for HPV detection because it is an extremely sensitive test that provides information on the presence of 29 individual HPV types and one group of 10 less common HPV types. In addition, PCR detects both high- and low-level infection. We will do type-specific classification to determine the various prevalences of HPV types. We will then be able to analyze our results for individual HPV types and will group them according to their association with cancer, as measured in a large international study of cervical cancer 62.

**HPV testing protocols.** HPV testing will be performed in the laboratory of co-investigator [name]. After collection, the brush for HPV testing will be placed in 1 ml of Sample Transport Medium (Digene Diagnostics, [name]). This quantity is more than sufficient to perform all HPV testing. The tubes will be transported to [name] lab. Two hundred µL of specimen are used for PCR. PCR is performed using MY09/MY11 consensus HPV L1 primers as well as primers for amplification of the human beta-globin gene. After 30 amplification cycles, 6 µL of amplification mixture are applied to a nylon membrane and probed with a biotin-labeled HPV L1 consensus probe mixture. A separate membrane is probed with a biotin-labeled probe to the human beta-globin gene. Specimens positive with the HPV consensus probe mixture are then studied to determine the specific HPV type by preparing membranes as described above with 6 µL of specimen. The membranes are studied with probes to 29 different HPV types (6, 11, 16, 18, 26, 31, 32, 33, 35, 39, 40, 45, 51, 52, 53, 54, 55, 56, 58, 59, 61, 66, 68, 69, 70, 73, AE2, Pap 155, Pap 291, as well as the following 10 HPV types together in a probe mixture: HPV 2, 13, 34, 42, 57, 62, 64, 67, 72, and W13B). Specimens that are positive with the generic probe, but negative for the 39 specific types are considered to have an "unknown" HPV type.

**Testing quality control.** [name] laboratory performs extensive quality assurance and quality control measures with each HPV assay. Because of its high sensitivity, PCR by definition must be performed with great care to avoid the possibility of contamination. The laboratory takes all possible precautions in handling samples, including separation of pre- and post-amplification products in different parts of the research building. Each run contains several random negative control specimens and positive controls for each HPV type being sought. His laboratory will also use HPV-positive tissue culture cells containing known numbers of HPV 16 copies as a sensitivity control. If any of the above negative and positive controls do not work, the reaction is repeated. The lab performs a large volume of HPV testing for several studies and to date has not had problems with contamination. Each specimen is also studied for the presence of beta-globin as a positive control for human DNA and for the overall amplification procedure. If a specimen is negative for beta-globin it is presumed that an inadequate specimen was obtained, that the reaction failed or that the specimen contained an inhibitor of the PCR reaction. In their experience this occurs in less than 5% of the specimens, and the HPV results from the specimen are excluded from analysis. As a final quality control measure, [name] laboratory participates in routine exchange of cervical specimens with the other laboratory performing PCR in the WIHS, the laboratory of [name]. The results of PCR detection are compared between the two labs, including the detection of specific types. In the past they have had excellent agreement and continue to do so.

For cytology quality control, a random sampling of 10% of normal and 100% of abnormal cytologic samples will be shipped to UCSF and reviewed by co-investigator [name] of the Department of Pathology at UCSF. Due to regulatory constraints in Zimbabwe, histologic specimens cannot be released for outside review.

**Definitions of abnormal tests.**  All cytologic specimens will be interpreted using the 1991 Bethesda System 63. As per standard practice, we will consider a Pap smear “abnormal” if interpreted as atypical squamous cells (ASCUS), low-grade squamous intraepithelial lesion (LSIL), atypical glandular cells (AGUS), high-grade squamous intraepithelial lesion (HSIL) or squamous cell carcinoma.

All HPV tests will be reported as positive for high-risk types, positive for low-risk types, positive for both, or negative for both. High-risk types will be defined as the presence of types 16, 18, 26, 31, 33, 35, 39, 45, 51, 52, 53, 56, 58, 59, 66, 68 and 73 33. Low-risk types will be defined as 6, 11, 40, 42, 54, 61, 70 and 72 33. If the beta-globin control is positive but no HPV is detected, the specimen will be considered “negative.”

**Statistical methods and analyses.** HPV prevalence will be estimated as the observed proportion positive, and associated precision summarized using a 95% exact binomial confidence interval. Incidence of HPV during follow-up will be investigated using survival analysis techniques appropriate for grouped or discrete time outcomes to account for intervals between visits. Initial analyses will include incidence over follow-up of particular types or groups of types among women confirmed to be negative at the baseline visit and will be summarized using life table estimates and 95% confidence intervals. We will use a similar approach in investigating persistence by examining differences in clearance among prevalent positives in both randomized groups. To accommodate repeated episodes of infection and clearance for high-risk types, we will also investigate the use of Markov models for panel data, taking negative and positive HPV tests at study visits as the observed states. These models will allow all available follow-up data to be used, provide direct estimates of the transition probabilities between positive and negative states and allow time-varying risk factors to be investigated using a proportional hazards model similar to those described above. Outcomes of viral load and cytologic and histologic abnormalities will be analyzed similarly.

For study aim #4, we will compare the prevalence rates of HPV (e.g., all HPV types, low-risk, types, high-risk types) between sero-converters and non-sero-converters using matched analysis controlled for confounders. We will separately evaluate the potential association between sero-conversion and HPV viral load using a 3-to-1 control-to-case ratio rather than the entire cohort of non-sero-converters since this assay is relatively expensive to perform.

**Statistical power.** For study aims #1-3, we calculated minimal detectable relative hazards for the main study outcomes based on the sample size of 2,200 enrollees with a 10% loss-to-follow-up rate, a power of 80% and a significance level of 5% (one-tailed alpha=0.05) using the log-rank test. We chose one-sided tests for this analysis since we do not believe that diaphragms increase risk of HPV outcomes. We performed analyses over a range of plausible prevalence rates of HPV (up to 40% for all types and as low as 20% for high-risk types) and evaluation periods (12 to 24 months). Prior studies of Zimbabwean sero-negative women have indicated a prevalence of HR HPV types of 28% 64. We assumed an annual HR HPV incidence rate of 8% and an annual clearance of 65% in the non-diaphragm arm based on studies from a high-risk area of Brazil 65. The prevalence of cytologic abnormalities was estimated at 15% and incidence at 10% per year in this high-risk population in the non-diaphragm arm. High-grade cervical intraepithelial neoplasia (CIN 2 or worse) prevalence was estimated at 5.9% based on a prior cross-sectional study in Zimbabwe 64. Assuming a cytology sensitivity of 62% 64 and an annual incidence rate of 0.5%, we estimated a prevalence of CIN 2 or worse of 3% by the end of the study in the non-diaphragm arm. For study aim #4, we assumed that 88 women would sero-convert to HIV-positive over the course of the study. We determined the minimal detectable odds ratios for a range of prevalence rates of predictors (e.g., HPV) at 80% power and one-tailed alpha of 0.05.

Table 1 details all power analyses for study aims #1-3. Under a variety of assumptions, we will have power to detect 16-37% reductions in incidence and persistence of HPV between the diaphragm group and the non-diaphragm group. We will also have power to detect at least a 26% reduction in incidence of cytological abnormalities. We will have less power to be able to detect differences in biopsy-proven CIN 2 or worse (a secondary study aim): a minimum 63% reduction with diaphragm use must be demonstrable for us to be able to detect a statistically significant effect. For study aim #4, we will have adequate power to detect differences in HPV prevalence between sero-converters (cases) and non-sero-converters (controls) if control prevalence rates are 20-40% and cases have at least 2.2 times the prevalence of HPV (Table 2). We believe that we will have adequate power for this analysis; a prior study, for example, has shown that in Zimbabwean women, the prevalence of HR HPV types is over two-fold greater in HIV-positive women (64%) compared to HIV-negative women (28%) 64. Our main hypothesis for study aim #4 involves evaluating a variety of predictors with various prevalence rates (e.g., all HPV types, low-risk, types, high-risk types), and we will have similar power to detect differences for other predictors in this range.

**Table 1:** Least detectable hazard ratios for various HPV-related outcomes over time assuming a sample size of 2,200 enrollees with a 10% loss-to-follow-up rate, a power of 80% and a one-tailed alpha=0.05)

| **Study Aim** | **Outcome** | **Baseline prevalence** | **Observation period (months)** | **Least detectable Relative Hazard** |
| --- | --- | --- | --- | --- |
| **#1** | **HPV incidence**  All types  High-risk types |  | | |
| 40% | 12 | 0.63 |
| 20% | 24 | 0.74 |
| **#2** | **HPV persistence**  All types  High-risk types |  | | |
| 40% | 12 | 0.77 |
| 20% | 24 | 0.84 |
| **#3** | **Cytologic abnormality incidence** | 15% | 24 | 0.74 |
| **Secondary** | **Cervical intraepithelial neoplasia incidence** | 4% | 24 | 0.37 |

**Table 2:** Study aim #4 power: least detectable odds ratios for risk factor prevalences of 10-40% assuming 88 sero-converters and 2,112 non-sero-converters (power=80%, one-tailed alpha=0.05)

| **Risk factor prevalence (e.g., HPV)** | **Least Detectable Odds Ratio** |
| --- | --- |
| 10% | 2.8 |
|  |  |
| 20% | 2.3 |
|  |  |
| 30% | 2.2 |
| 40% | 2.2 |

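### Appendix 16.2, Table 1: the detectable relative hazard of 0.37 for cervical intraepithelial neoplasia incidence does not follow from the stated 0.5% per year

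*Protocol*

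**What the plan says.** All of this is in Protocol Appendix 16.2 (HPV sub-study), in the paragraphs on statistical power and in Table 1. The common assumptions are 2,200 enrolled, 10% lost, 80% power, one-tailed alpha 0.05 and a log-rank test.

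For high-grade disease the baseline input is "High-grade cervical intraepithelial neoplasia (CIN 2 or worse) prevalence was estimated at 5.9" per cent. Combining a cytology sensitivity of 62% with the annual rate, the text takes "an annual incidence rate of 0.5%, we estimated a prevalence of CIN 2 or worse of 3% by the end of the study".

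Table 1 has a secondary row called "Cervical intraepithelial neoplasia incidence", with baseline prevalence 4%, observation period 24 months and least detectable relative hazard 0.37. The text comments: "We will have less power to be able to detect differences in biopsy-proven CIN 2 or worse (a secondary study aim", and then "a minimum 63% reduction with diaphragm use must be demonstrable for us to be able to detect a statistically significant effect".

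The row directly above is "Cytologic abnormality incidence", with 15% baseline prevalence, 24 months and 0.74. Its inputs are "The prevalence of cytologic abnormalities was estimated at 15% and incidence at 10% per year in this high-risk population".

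**The concern.** A row labelled as incidence, in a column of relative hazards, should follow from the annual incidence given for that outcome. The cytology row does. The intraepithelial neoplasia row does not, because 0.5% per year yields too few events for 0.37 to be detectable with 80% power.

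Read beside the other rows, 63% looks like the smallest preventive effect on new CIN 2 or worse that the sub-study could show. For new disease the true threshold is more extreme. Someone relying on the printed figure could take a null result as evidence that the diaphragm does not prevent new lesions, when the sub-study had little more than an even chance of detecting a 63% reduction in them.

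**Working it through.** **Inputs** (Appendix 16.2, statistical power and Table 1)

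- Women per arm: 2,200 x 0.9 / 2 = 990.
- One-sided alpha 0.05 (z = 1.645); power 80% (z = 0.842); (1.645 + 0.842)^2 = 6.18.
- CIN 2+: 0.5% per year for 24 months, so control risk = 1 - exp(-0.01) = 0.00995. Expected control events = 990 x 0.00995 = 9.9.

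**Formulas**

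- Total events D = n x [p0 + 1 - (1 - p0)^RH].
- Schoenfeld: power = Phi(|ln RH| x sqrt(D/4) - 1.645).
- Freedman: power = Phi(((1 - RH)/(1 + RH)) x sqrt(D) - 1.645).
- Simulation: binomial event counts in each arm, one-sided score test on the split of events.

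**Step 1. Does the method reproduce the table?** Cytology row, with the 15% prevalent women removed: n = 990 x 0.85 = 841.5 per arm and p0 = 1 - exp(-0.20) = 0.181. The least detectable RH is 0.738 (Schoenfeld) or 0.736 (Freedman), against 0.74 printed. The high-risk HPV row is less useful as a check. The text says "We assumed an annual HR HPV incidence rate of 8" per cent; that gives 0.733 with all 990 women kept, but 0.704 with the 20% prevalent women removed, against 0.74 printed. I rely on the cytology row only.

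**Step 2. Power at the printed 0.37, using 0.5% per year**

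| Control risk | Total events D | Schoenfeld | Freedman | Simulation |
|---|---|---|---|---|
| 0.00995 (all lesions detected) | 13.5 | 57% | 52% | 53% |
| 0.00617 (62% detected) | 8.4 | 42% | 38% | 38% |

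Removing the 4% with baseline disease (about 950 per arm) lowers the first row slightly, to 56% by Schoenfeld and 52% by simulation.

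**Step 3. What control risk does 0.37 need?**

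- Schoenfeld: D = 4 x 6.18 / (ln 0.37)^2 = 25.0.
- Freedman: D = 6.18 x (1.37/0.63)^2 = 29.2.
- Dividing by 990 x 1.37 gives a control risk of about 1.8% or 2.2%. With the 5.9% baseline cases removed, Freedman gives 2.3%.

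The range 1.8-2.3% over 24 months is roughly 0.9-1.2% per year, about twice the stated rate.

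**Step 4. Does the stated 3% prevalence give 0.37?** No. With p0 = 0.03 and 990 per arm the least detectable RH is 0.47 (Schoenfeld) or 0.45 (Freedman).

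**Step 5. Where might the figure come from?** This step is inference. At most about 1.0 point of the 3% can be new disease. Lesions missed at enrolment would be 5.9% x 0.38 = 2.24%, and 2.24% + 1.0% = 3.24%, near 3%. Likewise 5.9% x 0.62 = 3.66%, near the 4% in the table. If 62% of the exit lesions are then detected, 3% x 0.62 = 1.86%, which falls inside the range in Step 3. The protocol states neither the split nor a second use of 62%.

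**Step 6. What would be detectable for new disease alone?** At control risk 0.00995, Schoenfeld gives 0.24 and Freedman 0.15. In simulation RH 0.24 has only about 73% power, and 80% is reached near 0.19. At 62% detection Schoenfeld gives 0.15 (66% power in simulation), Freedman has no solution, and simulation reaches 80% near 0.07. At 18 months of follow-up, p0 = 1 - exp(-0.0075) = 0.0075, and Schoenfeld falls to 0.19 with all lesions detected.

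**The case against.** The strongest reply is that nothing is hidden. The power paragraph says that a 3% end-of-study prevalence was estimated, the 63% sentence speaks of biopsy-proven disease without using the word incidence, and the text warns of reduced power. Incidence could also be read operationally, as disease newly detected after a negative baseline test, which would admit lesions missed at enrolment.

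That reading may well be what was meant, and it is why relabelling is the first remedy offered. It does not rescue the figure. Table 1 still reports a relative hazard for incidence, the control risk behind it is not shown, and the one prevalence that is shown gives about 0.47. The warning of less power is itself expressed as 63%, which is too lenient a threshold for new disease.

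Three stronger readings are tempting, and the documents do not support them.

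- A reader might infer that the row was definitely built from missed plus new lesions with 62% applied twice. The arithmetic fits, but the working is not given. For the same reason I do not calculate how far full prevention of new lesions would move such a mixed outcome.
- A reader might take 0.24, or 0.15 at 62% detection, as the correct values. They rest on a large-sample formula at about 7-12 events, and fall short of 80% power when simulated.
- A reader might conclude that every other row calibrates cleanly. The high-risk HPV row matches only if prevalent women are kept in.

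**Conclusion.** The point holds as an inconsistency between a stated input and a stated result. At 0.5% per year, 990 per arm and one-sided 0.05, power at a relative hazard of 0.37 is about 53-57%, or about 38-42% with 62% detection, not 80%. For new CIN 2 or worse, the least detectable relative hazard is roughly 0.15-0.24 depending on the formula and about 0.19 by simulation. That means reductions of about 76-85%, where the text says 63%.

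This assumes full 24-month observation, as the table prints, and detection of every new lesion. Both are generous: Section 2 (Study Summary) gives an average of 18 months, and cytology sensitivity is put at 62%. That lesions missed at enrolment explain the gap is plausible but remains inference.

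Importance is low. This is a secondary outcome of a sub-study at one site, the row set no sample size, and the HIV endpoint is untouched. The result is no ground for doubting the power of the sub-study's main aims.

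**What to change.** Choose one of two corrections to the Table 1 row.

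- If the outcome is disease found by exit, relabel the row as CIN 2 or worse detected by exit, including lesions missed at enrolment, and print the control-arm risk that produced 0.37.
- If incidence is meant, replace 0.37 with a least detectable relative hazard for new disease of roughly 0.15-0.24. Name the formula, give about 0.19 by simulation, and note that it is lower still with 62% detection or with the average 18-month follow-up.

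In either case, add a sentence beside the 63% saying that it does not apply to new CIN and that a null result for this outcome is not evidence against prevention of new CIN.

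The cost is one row label or figure and one or two sentences. Visits, tests, sample size and analysis stay as they are.
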